#### Secondary outcomes

The secondary outcomes will include the levels of basic serum sex hormones [including luteinizing hormone (LH), follicle-stimulating hormone (FSH), oestradiol (E_2_), testosterone (T), progesterone (P), prolactin (PRL), dehydroepiandrosterone (DHEAS), and sex hormone binding globulin (SHBG)], the ovulation rate in each menstrual cycle, the clinical pregnancy rate, BMI, FAI, Ferriman-Gallwey scores, TCM syndrome scores and security index tests (including routine blood examination, routine urine and stool tests, hepatic and renal function, and ECG examination).

All the participants will be instructed to return to visit the doctor every week. They will be contacted by phone if they miss a scheduled appointment. All clinical progress, adverse events and additional medication use will be recorded at every visit.

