### Statistical analysis

Clinical data of all participants will be disposed in the final statistical analysis based on the intent-to-treat principle to determine the robustness of the evidence. The data processors will be unaware of the specific allocation situation. Basic indicators will be analysed to test the balance of each group at baseline. Comparisons will be processed based on changes from baseline to the end of the intervention and follow-up. The one-sample Kolmogorov-Smirnov test and graphical methods will be applied to test the normal distribution of continuous variables (such as the levels of basic serum sex hormones, HOMA-IR, ovulation rate, clinical pregnancy rate, BMI, FAI, Ferriman-Gallwey scores and TCM syndrome scores), which will be presented as the mean ± standard deviation if normally distributed and as the median with an interquartile range if not normally distributed. A paired *T* test or the Wilcoxon rank test will be used to compare variables within a group from baseline to the end of the intervention. Analysis of variance (ANOVA) with Bonferroni correction will be carried out to compare differences among groups of continuous variables consistent with a normal distribution. Continuous variables that do not meet the normal distribution will be processed by using the Kruskal-Wallis test followed by the Mann-Whitney *U* test. Categorical variables will be analysed by chi-square statistics when appropriate, and Fisher’s exact test will be used to compare discrete variables with fewer than 5 observations. All data analyses will be processed by the Statistical Package for Social Sciences (SPSS) version 25.0. A *P* value < 0.05 with a two-tailed test and mean difference with 95% confidence intervals will be considered statistically significant.

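### Clinical pregnancy, a yes/no outcome, is listed as a continuous variable, so its planned summary and baseline-change comparison carry almost no information

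*Protocol article*

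**What the plan says.** In the protocol article, Secondary outcomes lists "the ovulation rate in each menstrual cycle, the clinical pregnancy rate" with hormone levels, BMI, FAI and scores. Ovulation is thus expressed per cycle, and clinical pregnancy has no further definition.

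The Statistical analysis section then classifies the variables. It says "The one-sample Kolmogorov-Smirnov test and graphical methods will be applied to test the normal distribution of continuous variables", and its examples of such variables include both the ovulation rate and the clinical pregnancy rate ("continuous variables (such as the levels of basic serum sex hormones, HOMA-IR, ovulation rate, clinical pregnancy rate, BMI, FAI"). The listed variables are to be "presented as the mean ± standard deviation if normally distributed and as the median with an interquartile range if not normally distributed". For the between-group comparison, "Analysis of variance (ANOVA) with Bonferroni correction will be carried out to compare differences among groups of continuous variables" if they are normal; otherwise they are "processed by using the Kruskal-Wallis test followed by the Mann-Whitney" U test. The same section says that comparisons rest on changes from baseline to the end of the intervention and follow-up, and it plans paired within-group tests.

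A separate rule reads "Categorical variables will be analysed by chi-square statistics when appropriate", with Fisher's exact test for small counts. No outcome is named under it.

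Three other statements bear on the point. The inclusion criteria admit women with amenorrhoea, defined as an interval above 90 days. The exclusion criteria rule out pregnancy at entry. The analysis is declared to cover all participants by intention to treat.

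**The concern.** Pregnancy takes the value 0 or 1 in each woman, so a normality test, a median with IQR and a change from baseline do not describe it. If the word rate is read instead as one figure per arm, there is no distribution within an arm to test at all. Neither reading fits the continuous route.

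A reader of the trial report needs how many women conceived in each arm and how large the difference is, with its uncertainty. The continuous route yields neither. This is a rule that the article states, not a detail it leaves to a fuller document, and the suitable tests stand a few lines further on with no outcome attached.

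Ovulation raises a lesser question. A proportion of ovulatory cycles per woman can be ranked, but a rate per cycle is undefined (0/0) for a woman who has no cycle while under observation, and amenorrhoeic women are eligible. The article does not say how such a woman is scored.

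**Working it through.** **Inputs.** Sample size calculation section: 30 women per group, 38 after 20% attrition, five groups. Exclusion criteria: nobody is pregnant at baseline. Statistical analysis section: the sequence of normality test, summary and comparison set out above. The article gives no pregnancy rate, so the counts below are assumptions for illustration. It has no figure of its own on this point to reproduce, other than the group size: 30/(1 − 0.20) = 37.5, rounded up to 38, and 5 × 38 = 190, as stated.

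**Step 1: which branch does the rule take?** The Kolmogorov-Smirnov test was applied to 38 zeros and ones, with mean and SD taken from the data. The case least unfavourable to normality is 19/38:
- SD = √(0.25 × 38/37) = 0.507.
- The normal curve at 0 gives Φ(−0.5/0.507) = 0.162, while half of the data lie at 0.
- The largest gap is D = 0.500 − 0.162 = 0.338, which gives p = 0.0002.

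Every other count from 1 to 37 gives a p-value no larger. With 30 women per arm the largest p-value is 0.0015 (at 15/30). Normality is therefore always rejected, and the plan always goes to median (IQR) and rank tests.

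**Step 2: what would be reported?** Quartiles by linear interpolation at position (n − 1)p + 1:

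| Pregnant | % | Median | IQR |
|---|---|---|---|
| 4/38 | 11 | 0 | 0 to 0 |
| 8/38 | 21 | 0 | 0 to 0 |
| 9/38 | 24 | 0 | 0 to 0 |
| 10/38 | 26 | 0 | 0 to 0.75 |
| 15/38 | 39 | 0 | 0 to 1 |
| 19/38 | 50 | 0.5 | 0 to 1 |

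The median is 0 at any rate below 50%. The edge of the IQR depends slightly on the quartile convention. Interpolating at (n + 1)p puts the upper quartile at position 39 × 0.75 = 29.25; with 9/38 there are 29 zeros, so it becomes 0.25. At 8/38 (30 zeros) it is 0 under both conventions, so the 11% and 21% arms are reported identically either way.

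**Step 3: what is lost?** For 9/38 against 4/38:
- Risk difference = 0.237 − 0.105 = 0.132.
- Standard error = √(0.237 × 0.763/38 + 0.105 × 0.895/38) = 0.085.
- 95% CI = 0.132 ± 1.96 × 0.085, or −3.5 to 29.8 percentage points.

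The planned summary would show two identical lines instead.

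**Step 4: change from baseline.** With every baseline equal to 0, the change is the outcome itself. Subtracting baseline adds nothing, and a paired within-group test only compares the observed pregnancies with a column of zeros fixed by the entry criteria.

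**Step 5: is the overall test wrong?** Take assumed counts of 6, 8, 7, 10 and 14 out of 38:
- Chi-square = 5.82, p = 0.213.
- Kruskal-Wallis = 5.82 × 189/190 = 5.79, p = 0.215. On 0/1 data it equals chi-square × (N − 1)/N.
- ANOVA p = 0.215.

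The three agree closely. All five arms (16%, 21%, 18%, 26% and 37%) would nevertheless show a median of 0.

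**Step 6: ovulation.** No calculation is called for. Set side by side, the per-cycle definition, the eligibility of amenorrhoeic women and the intention-to-treat statement leave one case without a value: the woman with no observed cycle. The article does not give the share of such women.

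**The case against.** The strongest defence is that the rank test on 0/1 data is practically the chi-square test, so no false conclusion about pregnancy would follow from the overall p-value. That stands, and it confines the harm to the summary, the effect measure and the baseline-change comparison. It can also be said that the baseline-change sentence is general and does not name pregnancy. That is so, but the section makes no exception for it either. Chi-square and Fisher's test are already in the plan, so the correction amounts to moving one item between lists. This limits the severity without making the stated classification right.

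On ovulation, a reader might infer that women with no cycle are dropped, so that the worst responders vanish from the arm that failed them. The article does not say so: it declares all participants analysed by intention to treat and gives no exclusion rule. Nor does an interval above 90 days mean that no cycle occurs in six months. What stands is only that the value for such a woman is not fixed.

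A reader might also infer that cycles will be counted as independent observations, with an inflated type I error. The article does not describe that either. Treating ovulation as continuous points more naturally to one value per woman, for which a median and a rank test are legitimate. No error-rate figure can be attached to the plan on this ground.

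**Conclusion.** The point holds for clinical pregnancy: the article assigns a binary outcome to the continuous route. At 30 to 38 women per arm that route always ends in a median with IQR, which is 0 for any rate below 50% and 0 to 0 up to roughly a quarter of the arm, and it offers no usable effect estimate. Change from baseline is uninformative because pregnancy is excluded at entry. The size of the overall test is hardly affected.

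For ovulation the conclusion is narrower: the unit of analysis and the handling of women without a cycle should be made explicit. Neither selective removal of women nor inflated error rates can be read out of the document.

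The conclusion rests on pregnancy being recorded as yes or no per woman; the event counts are illustrative. Both outcomes are secondary. The primary HOMA-IR analysis and the sample size are untouched. The text should be corrected, but the point does not threaten the main result.

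**What to change.** **Clinical pregnancy.** Remove it from the continuous examples and name it under the categorical outcomes. Report the number pregnant over the number randomised in each arm, with risk differences and 95% CIs for the comparisons of interest. Test by chi-square or Fisher's exact test, with no baseline change and no paired test.

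**Ovulation.** Keep the outcome given under Secondary outcomes, but state that the woman is the unit of analysis, or use a model clustered by woman if cycle-level data are analysed. Keep women with no observed cycle in the intention-to-treat analysis as non-ovulating, for example through the proportion of women with at least one ovulation. That measure also does not penalise a woman who conceives early and so has fewer cycles afterwards, as a count of ovulations over a fixed period would.

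**Cost.** One paragraph in the Statistical analysis section. The tests for pregnancy are already in the plan, the follow-up already records pregnancy, and the sample size does not change. The visit schedule (Table 1) is not available to this review, so it should be confirmed that ovulation is recorded in a form that supports the per-woman measure.

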### Sample size calculation

The sample size calculated by Power Analysis & Sample Size (NCSS-PASS 11.0) was assessed based on HOMA-IR, which is the most significant outcome in this trial. In our pilot study (according to the research results of [name] doctoral thesis) evaluating the effect of metformin and BSHTD on HOMA-IR in patients with IR-PCOS, the results showed that HOMA-IR decreased from 2.11±0.30 to 1.71±0.26 in the metformin treatment group and the difference before and after treatment was 0.40±0.24, while HOMA-IR of Bushen Huatan Decoction combined with metformin treatment group decreased from 2.09±0.30 to 1.52±0.26 and the difference before and after treatment was 0.57±0.27. Therefore, we used the minimum sample size required to evaluate effectiveness [18]. We anticipate that after two courses of treatment, HOMA-IR of Bushen Huatan Decoction combined with metformin group will decrease by 30%, and HOMA-IR of single-use of metformin group will decrease by 20%. Therefore, the difference is 10%,with two-sided α assigned to be 5% and *β* 20% at the upper limit, respectively, at which the power is 90% and the rate of attrition estimated to be 20%. In a one-way ANOVA study, sample sizes of 30, 30, 30, 30, and 30 were obtained for the 5 groups whose means are to be compared. A total sample size of 150 subjects achieves 90% power to detect differences among the means versus the alternative of equal means using an F test with a 5% significance level. By enrolling 38 participants in each group, we allow the rate of attrition to be estimated to be 20%.

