### Randomization and allocation concealment

The eligible participants will be allocated into 5 groups at a ratio of 1:1:1:1:1. Researchers of the Department of Reproduction of Zhangjiagang TCM Hospital Affiliated to Nanjing University of Chinese Medicine will use a random number generator of the Statistical Package for Social Sciences (SPSS) version 25.0 to carry out the randomization process. The random sequences will be put into several opaque paper envelopes, numbered sequentially and then distributed to clinical researchers and doctors [19]. When new patients are recruited in this trial, the opaque paper envelopes will be opened to decide their distribution; moreover, the researchers will arrange the corresponding interventions for the patients. All procedures above will be maintained and followed as appropriate.

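### Plain Bonferroni after the ANOVA is valid, but Holm's step-down gives the same 5% family-wise guarantee with a little more power, whichever pairs form the family

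*Protocol article*

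**What the plan says.** The Statistical analysis section of the protocol article gives one rule for between-group comparison of normally distributed outcomes: "Analysis of variance (ANOVA) with Bonferroni correction will be carried out to compare differences among groups of continuous variables". It gives neither the number of comparisons nor the divisor for alpha.

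The Randomization section has participants "allocated into 5 groups at a ratio of 1:1:1:1:1", so ten pairs are possible. The Discussion lists a shorter set of hypotheses: B equivalent to A, D superior to A, E superior to B and to C, and E equal to D. That is five contrasts. The Statistical analysis section does not link the Bonferroni correction to them.

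The Sample size section rests on the overall F test: "A total sample size of 150 subjects achieves 90% power to detect differences among the means". Its pilot inputs are the falls in HOMA-IR. On metformin alone "the difference before and after treatment was 0.40±0.24", and on the decoction with metformin "the difference before and after treatment was 0.57±0.27".

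**The concern.** The superiority claims in the Discussion will be decided by pairwise tests, while the 90% power belongs to the overall F test. Under any multiplicity correction, power for a single pair at 30 per arm is well below 90%, so the efficiency of the correction matters.

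Plain Bonferroni holds every comparison to alpha/m. Holm orders the P values and tests the smallest at alpha/m, the next at alpha/(m−1), and so on, stopping at the first failure. Its first threshold equals Bonferroni's and each later one is more lenient. It therefore rejects everything that Bonferroni rejects and sometimes more, with the same control of family-wise error. This holds for any family and any correlation between the tests. What is at stake is a few points of power that need no extra patients.

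**Working it through.** **Inputs.** From the Sample size section: falls of 0.40 ± 0.24 and 0.57 ± 0.27, 30 analysed per arm, two-sided 5%. Difference = 0.57 − 0.40 = 0.17. Pooled SD = √((0.24² + 0.27²)/2) = √0.06525 = 0.2554. Error df = 150 − 5 = 145. The article gives means for two regimens only. The other three are assumed from the Discussion's hypotheses: A = B = C = 0.40 and D = E = 0.57.

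**The plan's own figure.** The grand mean is (3 × 0.40 + 2 × 0.57)/5 = 0.468. The sum of squared deviations is 3 × 0.068² + 2 × 0.102² = 0.03468. The noncentrality is 30 × 0.03468/0.06525 = 15.9, and the F-test power is 90.1%. The smallest n for 90% is 30 per arm, and 30/0.8 = 37.5 gives 38 per arm, 190 in total. The stated size reproduces under this pattern. It does not under others: power is 73% if only one arm is at 0.57, and 50% if three arms lie midway.

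**One pair, single-step methods.** The standard error of a difference is 0.2554 × √(2/30) = 0.0660, so the noncentrality is 0.17/0.0660 = 2.58. Critical values are t(1 − 0.05/(2m)) for Bonferroni over m comparisons and q(0.95; 5, 145)/√2 for Tukey.

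| Method | Critical t | Interval half-width | Power for 0.17 |
|---|---|---|---|
| Bonferroni, ten pairs | 2.851 | 0.188 | 39.6% |
| Tukey | 2.762 | 0.182 | 43.0% |
| Bonferroni, five contrasts | 2.610 | 0.172 | 48.9% |

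Bonferroni's critical value is 2.729 for seven comparisons and 2.775 for eight. Tukey is therefore the less conservative of the two only when eight or more of the ten pairs are tested.

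**Holm.** Its power depends on all the means, so it was simulated under the assumed pattern.

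| Family | Target | Bonferroni | Holm |
|---|---|---|---|
| Ten pairs | D v A | 39.6% | about 43% |
| Ten pairs | E better than both B and C | about 24% | about 28% |
| Five contrasts | D v A | 48.9% | about 53% |
| Five contrasts | E better than both B and C | about 33% | about 38% |

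**Error rate.** With all five means equal, simulated family-wise error for Bonferroni is 3.9% over ten pairs and 4.4% over the five contrasts. Holm's is the same in that case, because any rejection begins with the same first threshold. For Tukey it is 5.0% over ten pairs and 2.9% over the five contrasts.

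**The case against.** The strongest case against raising this is that Bonferroni controls the family-wise error for any set of comparisons, so the plan states nothing wrong, and choosing a slightly conservative method is a preference. The size of the family may also be set out in a document that is not shown. Both points stand: this is neither an error nor an omission. They do not touch the comparison with Holm, which is at least as powerful in every family.

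A reader might go further and infer that the plan spreads alpha over all ten pairs and that Tukey's test would be better at no cost. The documents do not support that. No ten-pair family is stated. The aim of finding the best scheme and the five-arm ANOVA make all pairs a possible reading, but the hypotheses in the Discussion amount to five contrasts. For those five, Tukey would widen intervals by 5.8% (2.762/2.610 = 1.058) and lower power from 48.9% to 43.0%.

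A further objection is that Holm has no simple matching simultaneous intervals. That is true, but it matters little here: the Statistical analysis section plans 95% intervals for mean differences and does not promise simultaneous ones.

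**Conclusion.** The point holds as a small efficiency gain. Replacing Bonferroni with Holm adds about 4 points of power for D versus A, and 4 to 5 points for showing E better than both B and C, with the same 5% guarantee. That Holm never rejects less is a general property and needs no assumption about the family.

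The sizes do rest on assumptions: 30 analysed per arm, the pilot SD, and a five-mean pattern of which the article supplies only two means. The pilot patients had mean baseline HOMA-IR of 2.11 and 2.09, below this trial's entry threshold of 2.29, so SDs and differences may not carry over. The absolute power figures are therefore illustrative.

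The change does not bring pairwise power near 90%, because the trial is sized on the overall F test. Nor can it establish the two equality hypotheses (B v A and E v D), since a non-significant difference test does not show equivalence under any correction.

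**What to change.** In the Statistical analysis section, replace the Bonferroni correction by Holm's step-down correction for the pairwise P values. State that it applies to the five contrasts in the Discussion: B v A, D v A, E v B, E v C and E v D. Keep the planned 95% confidence intervals for mean differences and label them as not adjusted for multiplicity. If all ten pairs are really to be tested, say so and use Tukey's test with its simultaneous intervals instead.

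The cost is one sentence. Holm needs only the unadjusted pairwise P values, sorted and compared with alpha/m, alpha/(m−1) and so on, and requires no extra patients or data. The drawback is that an unadjusted interval may exclude zero where the Holm-adjusted P value exceeds 0.05, so the report should say that significance is judged on the adjusted P value.

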### Outcome measurements

#### Primary outcomes

The primary outcomes are changes in HOMA-IR (calculated according to the fasting plasma glucose and serum insulin) and improvements in the oral glucose tolerance test (OGTT) and insulin-releasing test (INS).

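### Pairwise multiplicity is corrected only for normally distributed variables; a non-normal outcome, possibly HOMA-IR, has no stated correction, and its false-positive rate is about 16–19% over all pairs once some arms truly differ

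*Protocol article*

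**What the plan says.** The Statistical analysis section gives two routes for comparing continuous variables between groups.

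- Normal variables: ANOVA "with Bonferroni correction will be carried out to compare differences among groups of continuous variables consistent with a normal distribution".
- Other variables: "Continuous variables that do not meet the normal distribution will be processed by using the Kruskal-Wallis test followed by the Mann-Whitney" U test. No correction is mentioned.

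One threshold closes the section: a P "value < 0.05 with a two-tailed test and mean difference with 95% confidence intervals will be considered statistically significant". HOMA-IR is listed among the variables whose normality will be checked.

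On the number of arms: "The eligible participants will be allocated into 5 groups at a ratio of 1:1:1:1:1". The Discussion sets out five comparisons: B equal to A, D better than A, E better than B, E better than C, and E equal to D.

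On the primary outcomes: HOMA-IR change, "and improvements in the oral glucose tolerance test (OGTT) and insulin-releasing test (INS"). The Sample size section bases the calculation on "HOMA-IR, which is the most significant outcome in this trial", but no section gives a testing order, an alpha split or a rule that all three must succeed.

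**The concern.** Five arms give 10 pairs. With Bonferroni over all of them, each pair is tested at 0.05/10 = 0.005. On the non-normal route, read as written, each is tested at 0.05. The same comparison of the same outcome can thus face a tenfold difference in threshold, decided by a distribution check on the trial's own data.

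A significant Kruskal-Wallis result does not protect the pairwise tests that follow. With more than three groups, one truly different arm can open the gate, and the pairs that are truly equal are then tested with no allowance for their number. The trial aims to find the best of several schemes, so its conclusions rest on these pairwise results.

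A second, separate gap is that any of three primary outcomes could supply a positive claim.

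**Working it through.** **Inputs.** Five equal arms (Randomization section); 30 evaluable and 38 enrolled per arm, and pilot HOMA-IR changes of 0.40 (SD 0.24) for metformin and 0.57 (SD 0.27) for the combination with BSHTD (Sample size section); two-sided 0.05 (Statistical analysis section). Difference 0.57 − 0.40 = 0.17; pooled SD = √((0.24² + 0.27²)/2) = 0.2554; standardised effect 0.17/0.2554 = 0.67.

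**The plan's own figure.** The article states no family-wise error rate; its nearest figure is the sample size. The five means are not given. Assuming A = B = C = 0.40 and D = E = 0.57, in line with B = A and E = D in the Discussion, a noncentral F calculation at 30 per arm gives power 0.901, matching the stated 90%. Attrition: 30/(1 − 0.20) = 37.5, rounded to 38; 38 × 5 = 190. Other means give other sizes (45 per arm if only D differs), so this shows only that the pattern is compatible with the plan.

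**Error in the non-normal branch.** I simulated a Kruskal-Wallis gate at 0.05 followed by Mann-Whitney tests at 0.05, with 40,000 trials per setting, counting a false claim only between truly equal arms. Arms that differ do so by the pilot effect unless stated.

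| True pattern | All 10 pairs, n=30 | All 10 pairs, n=38 | Five named contrasts, n=30 |
|---|---|---|---|
| All five equal | 4.7% | 4.8% | 4.5% |
| A = B = C, D = E | 15.9% | 16.2% | 9.4% |
| Four equal, one differs | 18.5% | 19.5% | 8.3–14.5% |
| Four equal, one far apart | 20.6% | 20.6% | not run |

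In the third row the five-contrast figure depends on which arm differs: lowest if it is E (two of the five contrasts remain null), highest if it is C (four remain null). At 38 per arm the top of that range is 15.4%.

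**Check against theory**, with the gate always open:
- Four equal arms: P(studentized range of 4 > 1.96√2) = 20.3%.
- Split of three and two: 1 − (1 − 0.1223) × 0.95 = 16.6%.
- Only B–A and E–D null: 1 − 0.95² = 9.75%.

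**With correction.** Mann-Whitney at 0.005 for 10 pairs gives 3.0–3.1% if all arms are equal, 1.7–1.8% for A = B = C, D = E, and 2.3–2.4% with one arm different. At 0.05/5 = 0.01 for the five named contrasts (n=30) the results are 2.8%, 1.8% and 1.7–3.2%.

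**Three primary outcomes**, each held at 5%: 1 − 0.95³ = 14.3% if independent; 12.5% at correlation 0.5; 10.8% at 0.7. This is a different calculation and is not part of the 16–19%.

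**The case against.** **No correction stated is not the same as no correction intended.** The article never says that the Mann-Whitney tests are unadjusted or cover all 10 pairs, and an analysis plan not shown could add a rule. That stands as a limit. But the article does fix a correction in one sentence and leaves it off the parallel next one, under a flat 0.05. Followed as written, that rule is inconsistent.

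**The 5% level is not lost in every case.** A reader might infer that the error is always 16–19%. It is not: with all arms equal the gate keeps it near 5%, and if the outcome is judged normal the Bonferroni route applies. The figure needs both a partial null and a non-normal outcome.

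**All 10 pairs is more than the trial asks.** This stands, and is why the five-contrast range is given. Two of the five are equivalence statements, where a chance difference counts against the hypothesis. For the three superiority contrasts alone, the chance of a false result is about 4–8% with one arm different, and nil under A = B = C, D = E, because all three are then real.

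**Entry at HOMA-IR ≥ 2.29 does not make non-normality likely.** That inference is tempting, but the cut truncates baseline, while the analysis uses change. In an illustration with n = 30 and assumed values (lognormal baseline, median 2.6, log SD 0.4, truncated at 2.29; log treatment effect −0.25, SD 0.2), a Lilliefors test rejected normality in 64% of baseline samples but 14% of change samples. A plain Kolmogorov-Smirnov test with estimated parameters rejected in 0.1% of change samples. HOMA-IR can reach the uncorrected branch; the documents do not show that it will.

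**OGTT and INS without a named summary measure** is no defect here: an article may leave that detail to the full protocol.

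**Conclusion.** The inconsistency is real and lies in what the article states. For one outcome in the non-normal branch, the chance of at least one false pairwise difference is about 16–19% over all 10 pairs and roughly 8–14% over the five named contrasts at 30 per arm, against a nominal 5%. This assumes that the Kruskal-Wallis gate is respected, that the Mann-Whitney tests are run at 0.05, and that some but not all arms differ by about the pilot effect. The last is what the Discussion expects (B = A, E = D, D better than A).

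The documents do not support reading this as the trial's overall false-positive rate, or adding the three-outcome figure to it. The lack of a rule across the three primary outcomes is a smaller, separate gap. Its 14% is an upper figure, since HOMA-IR is computed from fasting glucose and insulin and independence from OGTT and INS is implausible.

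**What to change.** 1. State one multiplicity rule for both branches: Bonferroni or Holm over the same listed contrasts, whether the tests are parametric or rank-based. The five comparisons in the Discussion are the natural list; using all 10 pairs costs more power.
2. State how the three primary outcomes are judged. The Sample size section already puts HOMA-IR first, so test it first, and OGTT then INS only after it succeeds, within each contrast at that contrast's share of alpha. All three remain primary.

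No extra patients or data are needed, but the change should be made by amendment before unblinding. The cost is power in the non-normal branch. For D versus A at the pilot effect with 30 per arm, two-sample t-test power (as a guide) is about 72% at 0.05, 47% at 0.01 (five contrasts) and 38% at 0.005 (10 pairs). Holm recovers part of this. Under the ordered rule, OGTT and INS could not support a confirmatory claim on a contrast where HOMA-IR fails. A log scale, area-under-curve summaries or a sole primary outcome would be design choices and are not needed to close this point.

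### Bonferroni is stated only for the ANOVA branch: outcomes that fail the normality check go to Mann-Whitney tests at P<0.05 with no stated correction, and the mean-difference criterion does not fit a rank test

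*Protocol article*

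**What the plan says.** All references are to the protocol article.

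- **Randomization and allocation concealment:** "The eligible participants will be allocated into 5 groups at a ratio of 1:1:1:1:1".
- **Statistical analysis, normal branch:** "Analysis of variance (ANOVA) with Bonferroni correction will be carried out to compare differences among groups of continuous variables". The sentence goes on to limit this to variables consistent with a normal distribution. The number of comparisons corrected for is not given.
- **Statistical analysis, non-normal branch:** "Continuous variables that do not meet the normal distribution will be processed by using the Kruskal-Wallis test", followed by the Mann-Whitney U test. No correction is mentioned here. These variables are to be summarised by median and interquartile range.
- **Statistical analysis, closing rule, given once for everything:** P below 0.05, two-tailed, and "mean difference with 95% confidence intervals will be considered statistically significant".
- **Choice of branch:** a one-sample Kolmogorov-Smirnov test with graphical methods. HOMA-IR is among the variables to be checked.
- **Discussion:** the hypotheses amount to five comparisons: B with A, D with A, E with B, E with C, and E with D.

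**The concern.** Two consecutive sentences treat the same between-arm question differently. If an outcome passes the normality check, its pairwise comparisons are corrected. If it fails, the text sends it to pairwise rank tests under the general 0.05 rule. The strictness of the test then depends on a preliminary look at the data's shape and not on the question asked. This could affect HOMA-IR, which the Sample size calculation section calls the trial's most significant outcome.

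The closing rule adds a second mismatch. A mean difference with its interval is made part of the criterion without saying what the interval must show. For outcomes the plan has just declared non-normal, the Mann-Whitney test does not test a difference in means. The P value and the interval then address different quantities and can point different ways.

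At stake is a false claim that one of five regimens beats another.

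**Working it through.** **Inputs.** Five arms and two-sided 0.05 (quoted above). Evaluable size: "sample sizes of 30, 30, 30, 30, and 30 were obtained for the 5 groups whose means are to be compared". Enrolled size: 38 per arm, which reproduces as 30/(1 − 0.20) = 37.5, rounded up to 38, and 5 × 38 = 190. The plan states no family-wise error rate and no corrected threshold, so there is no figure of its own to reproduce on this point.

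**Step 1: number of comparisons.** Five arms give 5 × 4/2 = 10 pairs, so Bonferroni needs raw P < 0.05/10 = 0.005. For the five comparisons in the Discussion it needs 0.05/5 = 0.01.

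**Step 2: all five arms equal.** Pairs are reached only if Kruskal-Wallis gives P < 0.05, so the family-wise error cannot exceed the size of that test. Simulation (lognormal data, 4,000 replicates) gives 4.9% at 30 per arm and 5.2% at 38. The gate works in this case.

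**Step 3: one arm differs, four are equal.** The gate now opens because of the arm that truly differs. Four equal arms leave 4 × 3/2 = 6 true-null pairs, each tested at 0.05. With the gate open, the large-sample chance of at least one false positive is

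1 − (studentized range distribution function for 4 means at √2 × 1.960) = 20.3%.

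Simulation of the full procedure (Kruskal-Wallis gate, then uncorrected Mann-Whitney; lognormal data; 4,000 replicates per row; shift of the differing arm in SD on the log scale):

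| Per arm | Shift | Gate opens | False positive among the four equal arms |
|---|---|---|---|
| 30 | 0.5 SD | 43% | 15.2% |
| 30 | 1.0 SD | 98% | 19.6% |
| 38 | 0.5 SD | 53% | 16.2% |
| 38 | 1.0 SD | 99% | 20.1% |

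**Step 4: the same pairs with correction.** At 0.005 the formula, with critical value 2.807, gives 2.6%. Simulation at a 1.0 SD shift gives 2.1% (30 per arm) and 2.7% (38 per arm).

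**Step 5: only the five named comparisons.** Setting one arm apart leaves between two true-null pairs (arm E differs: B–A and D–A) and four (arm C differs: B–A, D–A, E–B and E–D). Uncorrected, the error is at most 2 × 0.05 = 10% to 4 × 0.05 = 20%. At 0.01 each it is at most 2% to 4%.

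**Step 6: the ANOVA branch, for contrast.** Ten Bonferroni-corrected pairs under equal means give a family-wise error of 3.9% at 30 per arm (145 error df) and 4.0% at 38 (185 df). That branch is controlled as written.

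**The case against.** **The gate is a correction.** A significant Kruskal-Wallis test is required first. This stands only when all arms are equal (step 2). The plan does not expect that: the Sample size calculation section anticipates a 30% fall in HOMA-IR with the combination of decoction and metformin, against 20% with metformin alone.

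**This is detail for the analysis plan.** How many comparisons the correction covers, and whether intervals are simultaneous, is commonly settled there, and I do not count either as missing. The point is narrower. The article itself states the correction for one branch and limits it to that branch. It then specifies the follow-up tests of the other branch and a general 0.05 rule. A separate analysis plan may close the gap, but this text does not.

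**The mean-difference interval may be meant only for the normal branch.** This is possible, since non-normal variables are summarised by medians. But the closing sentence makes no exception, and no effect estimate is named for rank-tested outcomes. Applied jointly with the Mann-Whitney P, the interval might trim the 20% somewhat. The text does not say what the interval must show, so that cannot be computed.

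**A stronger reading that does not hold.** A reader might infer that ordinary 95% intervals stand as a rival to the Bonferroni P values, and that the plan therefore runs at about 28% family-wise error. That figure (28.3% at 30 per arm) is correct only if unadjusted intervals alone, without any overall test, decided all ten pairs. The article never calls the intervals unadjusted, and Bonferroni-adjusted 95% intervals would agree exactly with the P values. The closing rule also joins the two criteria with *and*, so in the ANOVA branch the Bonferroni P decides and the error stays near 3.9%.

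**Conclusion.** The ANOVA branch is adequately protected as written. The rank branch is not: it has no stated correction, and the general criterion does not match its tests. The chance of a false positive among four equal arms is about 20% when the fifth differs clearly and all pairs are tested. It is about 15% to 16% when the fifth differs by half an SD, and at most 10% to 20% if only the five named comparisons are made.

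These figures assume 30 to 38 per arm, lognormal data with equal spread, and Mann-Whitney tests each judged at 0.05 after a significant Kruskal-Wallis test. They matter only for outcomes that fail the normality check, and whether HOMA-IR will is not known in advance. The article does not support a claim that the plan as a whole has 28% family-wise error. The point should be corrected, but it does not undermine the design.

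**What to change.** Reword the Statistical analysis section so that:

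1. The Mann-Whitney tests carry the same Bonferroni correction as the ANOVA comparisons, with the number of comparisons stated: raw P < 0.005 for all ten pairs, or < 0.01 if limited to the five in the Discussion.
2. Significance is declared on the adjusted P alone.
3. Rank-tested outcomes are reported with a Hodges-Lehmann shift in place of a mean difference.
4. Intervals in both branches are at the level matching the correction (99.5% individual intervals for ten pairs, 99% for five) and are labelled as simultaneous.

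This takes a few sentences and no extra data. The price is precision and power. For mean differences at 145 df, matching intervals are 2.851/1.976 = 1.44 times as wide for ten pairs and 1.32 times for five. As a guide to power, take the pilot changes in the Sample size calculation section: difference 0.57 − 0.40 = 0.17, pooled SD √((0.24² + 0.27²)/2) ≈ 0.255, and 30 per arm. The standardised difference is 0.17/(0.255 × √(2/30)) = 2.58. Normal-approximation power per pair is then about 73% at 0.05 (2.58 − 1.96 = 0.62), 50% at 0.01 (2.58 − 2.58 = 0) and 41% at 0.005 (2.58 − 2.81 = −0.23). That is a reason to limit the correction to the five comparisons the trial sets out to make.
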